## Materials & methods

### Design

The Standard Protocol Items: Recommendations for Interventional Trials (SPIRIT) flow diagram schedule of enrolment, interventions and assessment procedures is provided in Fig 1 [38]. We will conduct three concurrent ‘helix’ randomised controlled trials (Figs 2–4), as approved by Monash University Human Research Ethics Committee on the 8^th^ April 2022 (HREC 30698). The Helix design is a counterbalanced, randomised controlled trial that involves allocating participants to each level of an intervention, but spread across different context areas. The outcome measure is repeated for each intervention level / context area exposure, allowing for a pooled analysis with repeated measures within participants. This enhances statistical power of an investigation while minimising the risk of intervention-level contamination by separating them across the different context areas.

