**Fig 4 pone.0280865.g004:**
[figure not shown]
Visual representation of the helix randomised control trial design for Trial 3. C1 denotes combination 1, C2 denotes combination 2, Individual participants are exposed to the combinations of intervention level / context areas within a vertical combination column.

In trial 1, we will combine the ‘helix’ approach with factorial allocation of intervention levels. In all trials we will be using Latin-square sequencing of the intervention levels to minimise the risk of order effects from potentially biasing the contrasts between intervention levels. Participants will be exposed to context areas in a set order (meaning that order effects could impact contrasts between them) as comparisons between contexts are not of primary interest in these investigations.

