### Procedure

Vulnerable subgroup populations will be recruited from partner organisations listed in Table 2. An advertisement via email, in person or via the partner organisation social media pages will be used, explaining the basic details of the project and what is required. A link to the explanatory statement and survey will also be included in this advertisement and participants will be able to complete the survey independently in their own time, with assistance from a family member or carer, or with assistance from a member of the corresponding partner organisation team if completing the survey on site. All information (explanatory statements, survey questions and video information) will be captioned, translated, interpreted or adapted accordingly to the communication profiles of the different vulnerable subgroup populations. This includes Auslan for the deaf and hard of hearing group, and Dari and Sinhalese for the refugee and asylum-seeker group. The general community group will be recruited online using social media platforms (i.e. Facebook and Twitter).

**Table 2 pone.0280865.t002:** Partner organisations related to each subgroup population.

Vulnerable Subgroup	Partner Organisation
**People living with a disability and their carers**	Able Australia, Wallara and Yooralla
**Aged care workers**	Donwood Community Aged Care Services
**Refugee and asylum seekers**	enliven
**Deaf, hard of hearing people**	Expression Australia and Able Australia
**Aboriginal and Torres Strait Islander peoples**	Peninsula Health
**Street-based sex workers**	St Kilda Gatehouse
**General Australian community**	Not applicable.

Randomisation will occur automatically via the inbuilt randomisation function on the Qualtrics data collection platform (Qualtrics, Provo, UT, USA). Therefore, random allocation will be fully concealed from participants and investigators involved in recruitment and data collection.

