### Study timeline

Participants will be able to access the relevant survey (to their subgroup) leading to either Trial 1 then Trial 3 (combined) or Trial 2 then Trial 3 (combined) independently or with assistance from the corresponding Partner Organisation. By following the link to the corresponding survey for each subgroup population, participants will have access to the explanatory statement including inclusion and exclusion criteria. From there, participants can choose to participate and confirm they adhere to the inclusion criteria. The data collection and survey builder software Qualtrics (Qualtrics, Provo, UT, USA) will automatically, randomly allocate participants into one of four potential combinations of allocation using a Latin Square approach for both Trial 1 and Trial 2, (minimising study level order effects), and will again randomly assign to one of two possible combinations for Trial 3. Data will be extracted for analysis purposes with no follow-up period required. Refer to Fig 1 for an overview of the study timeline.

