### Analysis

The comparisons we will undertake across the three trials will be:

#### Trial 1

Main effect of who is providing the message (General Practitioner versus community representative).Main effect of visual stimulus (talking head versus animation).Interaction effect between these two main effects.Simple effects if interaction effect is significant.

#### Trial 2

General practitioner talking head visual stimulus delivered health message versus animated general practitioner visual stimulus delivered health message.Politician visual stimulus delivered health message versus general practitioner talking head visual stimulus delivered health message.Written delivery of health message (control) versus all other intervention types (general practitioner talking head, general practitioner animation and politician delivered health message).

#### Trial 3

The effectiveness of health information provision delivered through a conversational training approach by a general practitioner versus through a direct information provision approach by a general practitioner.

Comparisons will not be made between context areas as part of the primary analysis. However, we will investigate interaction effects of the different intervention comparisons across the different context areas and population subgroups so that we can understand whether certain interventions work better in certain contexts and populations.

Linear mixed model analyses will be used treating the intervention levels as fixed factors and participants as random factors. Context will be ignored when investigating intervention main effects as it will be balanced across the different intervention levels.

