### Sample size

The repeated-measures, latin square design creates an analysis paradigm comparable to a paired-sample comparison of proportions. The least statistical power generated through the helix design arises when there is a simple contrast between two levels of an intervention within a singular vulnerable group category. Power analysis for this context can be approximated by a power analysis conventionally performed for McNemar’s Test, though we will be using linear mixed models for our analyses. A sample size of 36 participants per subgroup will provide 80% to detect a difference in proportions of respondents being “more inclined” or “much more inclined” with a primary outcome statement from 0.2 to 0.4. This assumes a correlation between the outcome proportions of (0.61) and a two-tailed alpha of 0.05. We aim to recruit 40 participants per vulnerable subgroup to allow for ~10% partial completion of the full survey. The study is conducted in a single session so there is no further allowance for loss to follow-up (this is irrelevant in our context). No maximum sample size will be set for the community sample given our online recruitment approach and short time-frame for data collection negating the need to cease the trial “early” due to important findings being identified.

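### Leaving context out of the intervention main-effect models because it is balanced avoids bias but gives up precision; a fixed context term recovers it at almost no cost

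*Protocol article*

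**What the plan says.** The Analysis section fixes the model: "Linear mixed model analyses will be used treating the intervention levels as fixed factors and participants as random factors". It then sets context aside: "Context will be ignored when investigating intervention main effects as it will be balanced across the different intervention levels". Context comes back only in separate analyses, where "we will investigate interaction effects of the different intervention comparisons across the different context areas and population subgroups".

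Three features of the design matter here.

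- The Design section describes a layout that "involves allocating participants to each level of an intervention, but spread across different context areas". Within a trial, each participant therefore meets each intervention level in a different context.
- The same section adds: "Participants will be exposed to context areas in a set order (meaning that order effects could impact contrasts between them". Context and survey position are thus one factor.
- The Study timeline section says the software will "randomly allocate participants into one of four potential combinations of allocation using a Latin Square approach for both Trial 1 and Trial 2", with two combinations in Trial 3.

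The Sample size section rests on a McNemar approximation for a two-level contrast within one subgroup: 36 participants, raised to 40 "to allow for ~10% partial completion of the full survey". It has no term for differences between contexts.

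**The concern.** The reason given supports a weaker conclusion than the one drawn from it. In a balanced Latin square the context effects cancel out of the intervention contrast, so the estimate is the same with or without a context term. The error term is a separate matter. Each within-participant difference between two interventions is also a difference between two contexts, and a participant random effect removes only what is constant within a person. Variation between contexts therefore stays in the residual unless it is modelled, and removing it is part of what the analysis of a Latin square is for.

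The Design section justifies the helix layout partly by its gain in power, and the Analysis rule returns some of that gain. The Discussion would treat similar effects of general-practitioner and community-leader messages as grounds for producing fewer group-specific materials, so an avoidable loss of precision bears on how a null result would be used.

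**Working it through.** **The plan's own figure.** Inputs from the Sample size section: proportions 0.2 and 0.4, correlation 0.61, two-sided alpha 0.05.

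- p11 = 0.2×0.4 + 0.61×√(0.2×0.8×0.4×0.6) = 0.1995
- Discordant proportion D = 0.6 − 2×0.1995 = 0.2009
- n = [1.96√0.2009 + 0.842√(0.2009 − 0.04)]² / 0.04 = 36.98
- Power at n = 36 is 78.9%; 36/0.9 = 40

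The stated 36 and 40 are reproduced to within one participant.

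**Assumptions, none given in the protocol.** Residual variance σ² = 0.5 on the 5-point scale. The SD of the four context means, s (root mean square deviation, divisor 4), is 0.2, 0.4 or 0.6. The effect is 0.465, chosen to give 79% power with context modelled.

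**Residual with context ignored** (n = 36, four contexts). Residual df = 4n − 1 − (n − 1) − 3 = 105. The expected mean square is σ² + n×4s²/105. At s = 0.4 this is 0.5 + 36×0.64/105 = 0.719. The pairwise SE becomes √(2×0.719/36) = 0.200, against √(2×0.5/36) = 0.167 with context modelled, a ratio r of 1.20.

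**Power.** Let k = 0.465/0.1667 = 2.79 and t = 1.98.

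- Combinations evenly filled: the true SD of the estimate stays at 0.167 and only the reported SE grows. Power = Φ(k − t·r); type I error = 2Φ(−t·r).
- Simple randomisation: the reported SE is about right and the estimate itself is noisier. Power ≈ Φ(k/r − t); type I error is about 5%.

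| s | r | Power, even | Type I, even | Power, simple |
|---|---|---|---|---|
| 0.2 | 1.05 | 76% | 3.7% | 75% |
| 0.4 | 1.20 | 66% | 1.7% | 63% |
| 0.6 | 1.41 | 50% | 0.5% | 50% |

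Simulations of the 4×4 square (4,000 replicates per cell) agree. At s = 0.4 with even filling, the model SE is 0.199–0.200 against a true SD of about 0.166, with power 66–67%. Under simple randomisation the model SE is 0.198 against a true SD of about 0.197, type I error is about 4.5–5% and power about 65%. At s = 0.6, simulated power lay between 47% and 51%. With context as a fixed effect, power stayed at about 78–80% and type I error near 5% throughout.

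**Trial 1 main effects.** These average two cells per level, so the SE with context modelled is √(0.5/36) = 0.118 and k = 3.95. For the same effect in one subgroup, power is about 97% with context modelled. With context ignored at s = 0.2, 0.4 and 0.6 it is 97%, 94% and 87% (even) or 96%, 90% and 79% (simple). The SE ratio is unchanged; these contrasts simply start with more power.

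**Pooled over six subgroups** (n = 6×36 = 216). Even the pairwise contrast has k = 2.79×√6 = 6.83. At r = 1.41 power is Φ(6.83/1.41 − 1.96), over 99%.

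**Trial 3** (two contexts, two combinations). r = √(1 + g²/2), with g the difference between contexts in residual SDs. Starting from 80%, g = 0.5, 1.0 and 1.5 gives about 76%, 66% and 48% (even) or 75%, 63% and 48% (simple).

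**Cost of the term when contexts do not differ.** None with even filling; about 1 to 2 power points under simple randomisation.

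**The case against.** Much of the case for leaving the plan alone stands.

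- **The magnitudes are assumed.** The protocol gives neither a context SD nor a residual variance. With equally spaced contexts, SDs of 0.4 and 0.6 mean gaps of about 1.1 and 1.6 points between best and worst, which is large on a 5-point scale. If the SD is defined with divisor 3, r falls to 1.04, 1.15 and 1.32.
- **The outcome is anchored on change.** The Outcomes section asks whether people are less or more inclined after viewing. Contexts that differ in baseline acceptance need not differ on this scale.
- **The steepest losses are not in the headline Trial 1 comparisons.** Pairwise cell contrasts in Trial 1 arise as simple effects, examined only if the interaction is significant. However, the Sample size section itself names the single-subgroup, two-level contrast as the least-powered case, and the Trial 3 comparison within a subgroup is of that kind.
- **Context is recorded and will be modelled in the interaction analyses.** This is true, but those analyses do not change the main-effect models, for which the text states an explicit rule.

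Three stronger readings are tempting and not supported. A reader might infer that the standard error is overstated and, in addition, that chance imbalance adds noise. These are alternatives: once imbalance adds noise, the reported SE is about right. A reader might infer that allocation will be uneven, since simple randomisation of 36 to four combinations leaves the largest and smallest differing by 6 or more in 57% of subgroups. The Procedure section says only "Randomisation will occur automatically via the inbuilt randomisation function on the Qualtrics data collection platform"; whether the setting fills combinations evenly is a detail an article may omit. A reader might also infer that results will be biased or the 80% target missed. Neither follows: nothing here inflates type I error, and the loss is relative to the same model with context included.

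**Conclusion.** The point holds as an avoidable loss of precision of unknown size. Balance justifies an unbiased estimate, not the omission of the factor from the error model. With even filling the test is conservative; with uneven filling the estimate is noisier; power falls in both cases if contexts or survey positions differ in mean response.

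Under the stated assumptions, a pairwise contrast in one subgroup of 36 loses 2 to 4 points of power at a context SD of 0.2, about 13 at 0.4 and roughly 30 at 0.6, and nothing if contexts do not differ. Single-subgroup pairwise contrasts, Trial 3 included, are the most exposed; Trial 1 main effects are less so, and analyses pooled over subgroups hardly at all. Because there is no bias and no excess of false positives, this should be fixed but does not threaten the validity of the trials.

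**What to change.** Replace the sentence that sets context aside with: 'Context (four levels in Trials 1 and 2, two in Trial 3) will be included as a fixed effect in every intervention main-effect model, with participant as a random effect; contexts will not be compared in the primary analysis.' Keep the intervention-by-context interactions as separate analyses, as now planned.

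The cost is 3 degrees of freedom out of 105 in a subgroup of 36, or 1 in Trial 3. No new data are needed. Because contexts come in a set order, the same term also removes survey-position effects.

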### Sample size

The repeated-measures, latin square design creates an analysis paradigm comparable to a paired-sample comparison of proportions. The least statistical power generated through the helix design arises when there is a simple contrast between two levels of an intervention within a singular vulnerable group category. Power analysis for this context can be approximated by a power analysis conventionally performed for McNemar’s Test, though we will be using linear mixed models for our analyses. A sample size of 36 participants per subgroup will provide 80% to detect a difference in proportions of respondents being “more inclined” or “much more inclined” with a primary outcome statement from 0.2 to 0.4. This assumes a correlation between the outcome proportions of (0.61) and a two-tailed alpha of 0.05. We aim to recruit 40 participants per vulnerable subgroup to allow for ~10% partial completion of the full survey. The study is conducted in a single session so there is no further allowance for loss to follow-up (this is irrelevant in our context). No maximum sample size will be set for the community sample given our online recruitment approach and short time-frame for data collection negating the need to cease the trial “early” due to important findings being identified.

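### The 80% power at 36 per subgroup assumes the largest correlation that proportions of 0.2 and 0.4 allow, so for single-response subgroup contrasts it is a best case

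*Protocol article*

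**What the plan says.** The Sample size section treats the repeated-measures Latin square as comparable to a paired comparison of proportions. It says that power is lowest "when there is a simple contrast between two levels of an intervention within a singular vulnerable group category", and that "Power analysis for this context can be approximated by a power analysis conventionally performed for McNemar’s Test", although linear mixed models will be used for the analysis.

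The claim itself is: "A sample size of 36 participants per subgroup will provide 80% to detect a difference in proportions of respondents" who answer in the top two categories "with a primary outcome statement from 0.2 to 0.4". The section then gives the assumption: "This assumes a correlation between the outcome proportions of (0.61) and a two-tailed alpha of 0.05". It offers no source for 0.61 and no other value. Recruitment is set at 40 per vulnerable subgroup to allow for about 10% partial completion.

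On what forms a pair, the Design section says that the helix design "involves allocating participants to each level of an intervention, but spread across different context areas". On the analysis, the Analysis section says: "Linear mixed model analyses will be used treating the intervention levels as fixed factors and participants as random factors".

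**The concern.** In a paired comparison of proportions, the correlation fixes how many participants respond to one message but not the other, and hence the power. For given proportions it has an upper limit. The assumed 0.61 sits at that limit.

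Two things make this matter. First, the text introduces the calculation as the least-power situation, so a reader will take 80% as a minimum that other contrasts exceed. For a single-response contrast it is close to the most that the formula can give. Second, the two answers in a pair concern different behaviours, for example a booster vaccine and QR check-in in Trial 1, or asking home workers about vaccination and not sharing food in Trial 3. A correlation at the limit requires almost everyone who is inclined under the weaker message on one behaviour to be inclined under the stronger message on another.

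The figure sets recruitment in all six vulnerable groups. The Analysis section plans to look at intervention effects by population subgroup, and the Discussion considers that a similar effect of a general practitioner's message across groups could reduce the need for group-specific media. How much weight a null result in one subgroup can bear depends on its power.

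**Working it through.** **Inputs, all from the Sample size section.** p1 = 0.2, p2 = 0.4, difference d = 0.2, correlation φ = 0.61, two-sided alpha 0.05 (z = 1.96), power 80% (z = 0.8416), n = 36.

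**Upper limit of the correlation.** φ_max = (min(p1, p2) − p1·p2) / √(p1·q1·p2·q2), with q = 1 − p
= (0.2 − 0.08) / √(0.2 × 0.8 × 0.4 × 0.6) = 0.12 / 0.19596 = 0.6124.

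**Cells at φ = 0.61.**
- Inclined under both: 0.08 + 0.61 × 0.19596 = 0.1995.
- Inclined only under the weaker message: 0.2 − 0.1995 = 0.0005.
- Inclined only under the stronger message: 0.4 − 0.1995 = 0.2005.

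Among 36 participants, 36 × 0.0005 = 0.02 people are expected to respond only to the weaker message.

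**Reproducing the plan's figure.** Connor's formula for McNemar's test, with discordant total pd = 0.2009:
n = [1.96·√pd + 0.8416·√(pd − d²)]² / d²
= [1.96 × 0.4483 + 0.8416 × 0.4012]² / 0.04 = 37.0.

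Power at 36 = Φ[(d·√36 − 1.96·√pd) / √(pd − d²)]
= Φ[(1.2 − 0.8786) / 0.4012] = Φ(0.80) = 78.9%.

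This agrees with 36 and 80% to within rounding. At the limit of 0.6124 the formula gives n = 36.8 and 79.1% power, so no correlation gives more at n = 36.

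**Lower correlations.** The protocol gives none, so these are assumptions shown as a range. The detectable difference is the one from 0.2 that gives 80% power at 36.

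| φ | only weaker | only stronger | power at 36 | n for 80% | detectable difference |
|---|---|---|---|---|---|
| 0.61 | 0.0005 | 0.2005 | 79% | 37 | about 20 points |
| 0.5 | 0.022 | 0.222 | 70% | 46 | 23 points |
| 0.3 | 0.061 | 0.261 | 57% | 61 | 27 points |
| 0 | 0.120 | 0.320 | 44% | 84 | 32 points |

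If all 40 recruits complete, power is 83%, 74%, 61% and 48% in the same order.

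**Other versions of McNemar's test at n = 36.** At φ = 0.61, enumeration gives 75% for the exact test, 87% for mid-p and 94% for the uncorrected chi-square. At φ = 0.5 these are 62%, 73% and 75%. Mid-p and the uncorrected test keep 80% only down to φ of about 0.56 and 0.53.

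**Which contrasts have one response per level.** In Trial 1 each participant sees each of the four factor combinations once, so a simple effect compares one response with one response, while a main effect averages two per level. In Trial 3 each participant sees each of the two arms once, so every subgroup contrast there is a single-response contrast.

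**The case against.** The strongest reply is that the plan's arithmetic is right and that McNemar's test is only a stand-in. The outcome has five categories, the analysis is a linear mixed model, and the leading Trial 1 comparisons are main effects with two responses per level. All of this stands. In a simulation with 36 participants and a five-point outcome driven by an assumed latent normal variable, Trial 1 main effects within one subgroup had 84–99% power at latent correlations of 0.3–0.6 with equal context rates. Eighty percent is therefore plausible for those effects without a correlation of 0.61. The same simulation gave 53–87% for contrasts with one response per level, so the five-point scale may recover some power there, but not dependably 80%.

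A second reply is that the result depends on the formula. It does near the limit, but at a correlation of 0.5 none of the versions tried reaches 80%.

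Two stronger readings are tempting. A reader might infer that the sample size was miscalculated; the inputs reproduce the output, so it was not. A reader might also infer that the design fails to deliver its power. The protocol gives no true correlation, and every value below 0.61 used here is an assumption, so a shortfall is likely but not shown.

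**Conclusion.** The point holds as a criticism of an unsupported planning assumption. The value 0.61 is the largest correlation that proportions of 0.2 and 0.4 permit, the protocol does not justify it, and the pairing of different behaviours makes it hard to defend. Under the formula that reproduces the plan's figure, about 79–80% is the ceiling at 36 completers for a single-response contrast within one subgroup, yet the text presents it as the worst case. Over assumed correlations of 0 to 0.5 the power is about 44–70%.

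This rests on the McNemar approximation that the plan itself chose. It applies to Trial 1 simple effects and Trial 3 within a subgroup. It does not extend to Trial 1 main effects, and it does not call for a different choice of primary contrast.

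**What to change.** In the Sample size section:

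- State that 0.61 is the upper bound of the correlation for proportions of 0.2 and 0.4.
- Replace the unqualified 80% with power, or the detectable difference, at 36 completers over a range of correlations. For example, correlations of 0 to 0.5 give about 44–70% power, or 32 down to 23 points.
- Say that these figures are for single-response contrasts within one subgroup, and that Trial 1 main effects, with two responses per level, have more power.

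This is a change of wording. It needs no more participants and no change to the analysis. The only cost is a less favourable stated power for single-subgroup contrasts.
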